### Statistical analysis

Changes in all endpoints will be assessed across groups (r-TMS plus VS and SHAM plus VS) and across time (at post-test and 12 weeks follow-up assessment). BIT, TAP, CBS, and the motor function tests (MI, TCT, and FIM^tm^) provide standard scores, separated for each test, and scores including a general performance with cutoffs that allow discriminating pathological performance. vABI and IHTT are continuous variables based on neurophysiological data. Differences in primary and secondary outcomes for each indicator will be analyzed between the pre-test baseline (T0), post-test(T1), and follow-up (T2) phases for both groups of patients (group r -TMS plus VS and SHAM plus VS group).

The pretest-posttest follow-up control group design is often analyzed with the posttest and follow-up as dependent variables and the pretest as covariate (ANCOVA) [34, 35] or with the difference between posttest and pretest as dependent variable (CHANGE) [36, 37]. The choice of one of these two methods should consider two assumptions: homogeneity vs. heterogeneity of the study population (i.e., group differences at pretest) and normal data distribution.

In general, ANCOVA is preferable in randomized controlled trials as treatment assignment is based on randomization [34–36], and this may prevent data heterogeneity. However, in heterogeneous data, a measure of gain is preferable (i.e., CHANGE). Both methods have more power if data are normally distributed [36].

In our study, we will verify first the two assumptions mentioned above for each outcome measure and, afterward, we will adopt the appropriate approach:

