Homogeneity vs. heterogeneity: For each outcome measure, the ANCOVA assumption of homogeneity of regression slopes will be verified [38]. In case the assumption is violated, a CHANGE measure (i.e., a score of gain in the specific outcome) will be considered in a 2 × 2 mixed-model ANOVA with the between factor group and the within factor time (posttest and follow-up).Normal distribution: Our primary outcome (the Behavioral Inattention Test) data will be analyzed after linear logistic transformation accordingly to the Rasch calibration, which ensures normal data distribution [39]. For the secondary outcomes, in the case normal distribution is not verified, a linear logistic transformation will be performed.In the case assumptions are verified, a mixed-model ANCOVA will be used with a 2 × 3 design, where the “between” factor will be the randomization group and the “within” factor will be the time of assessment, with the covariate pre-test baseline (T0) used to control for the LHN level before the beginning of the rehabilitation protocols.

In all cases, a two-tailed *t* test for independent samples will be employed to investigate the differences between groups. Data analysis will be performed using the MatLab (The Mathworks Inc.) and SPSS (version 13) softwares. We will accept a significance level of 5% (i.e., *p* value = .05) corrected for multiple comparisons when needed. Data from all randomized patients will be included in the analyses. Should data be missing at follow-up, data will be analyzed according to the intention to treat principle. However, participants will be contacted by telephone in the proximity of follow-up to ensure participant retention.

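### The main ANCOVA is specified as 2 × 3, which makes T0 both an outcome level and the covariate; this contradicts the rest of the section and rescales a time-averaged group effect by 2/3

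*Protocol article*

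**What the plan says.** All of this is in the Statistical analysis section of the protocol article.

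- **Main model**, used if the assumptions are verified: "a mixed-model ANCOVA will be used with a 2 × 3 design". Group is the between factor and time of assessment the within factor, "with the covariate pre-test baseline (T0) used to control for the LHN level before the beginning of the rehabilitation protocols".
- **Time points compared:** outcomes "will be analyzed between the pre-test baseline (T0), post-test(T1), and follow-up (T2) phases for both groups of patients". Table 1 shows no further assessment.
- **The ANCOVA as described earlier in the section:** this type of design is analysed "with the posttest and follow-up as dependent variables and the pretest as covariate (ANCOVA").
- **Fallback if regression slopes are not homogeneous:** change scores in a "2 × 2 mixed-model ANOVA with the between factor group and the within factor time (posttest and follow-up").
- **In all cases:** a two-tailed t "test for independent samples will be employed to investigate the differences between groups".

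The section does not say which term or contrast is the reported treatment effect, and it mentions no confidence interval.

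**The concern.** With three assessments, a three-level time factor must include T0. The baseline score is then predicted from itself at one of the three levels, where no group difference can remain after adjustment. Any quantity that pools over the levels takes in this built-in zero.

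Two results are affected. A group effect averaged over time would come out too small as a measure of the post-treatment effect. The group-by-time test would no longer ask whether the effect differs between T1 and T2. That question matters because the aims are immediate and long-term efficacy, and the Discussion expects the effect to persist at follow-up.

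The section also gives two incompatible structures for the main analysis of the primary endpoint, so two analysts following it could fit different models.

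**Working it through.** **1. Count the time levels.** The assessments are T0, T1 and T2. A 2 × 3 group-by-time design uses all three. The ANCOVA described earlier in the section uses T1 and T2 as outcomes, which is 2 × 2, and the fallback is 2 × 2 on the same two visits. The 2 × 3 statement is the odd one out.

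**2. Group main effect.** Let d1 and d2 be the T0-adjusted group differences at T1 and T2. Regressing T0 on group and T0 gives a group coefficient of 0 with no residual. Averaging over the levels:

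- 2 × 3 model: (0 + d1 + d2)/3
- 2 × 2 model: (d1 + d2)/2
- Ratio: (1/3)/(1/2) = 2/3, whatever d1, d2 or the correlations are.

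The residual of the subject mean is scaled by the same 2/3, so the standard error and interval width shrink equally and t, F and p stay the same.

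**3. Check on simulated data** (25 per arm, SD 3.1, assumed effects and correlations). One data set gave 2.16 (95% CI 1.48 to 2.84) from the 2 × 3 model and 3.24 (2.23 to 4.26) from the 2 × 2 model. The ratios of estimate, standard error and interval width were all 0.6667, and the adjusted difference at T0 was zero to rounding error. A random-intercept mixed model on 150 simulated trials gave ratios of 0.6667 (estimate) and 0.6668 (mean standard error), so the result does not depend on a classical repeated-measures fit.

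**4. An illustration in the protocol's own units.** The Sample size section gives 3.1, 2.84 and the constant 10.5. Its N is approximately reproduced when 3.1 is read as an SD and 2.84 as a difference: 2 × 10.5 × 3.1² / 2.84² = 25.02, against 25.2 stated; 25.2/0.9 = 28 per group. Read literally as variance and squared difference, it gives 2 × 10.5 × 3.1 / 2.84 = 22.92. I therefore use 2.84 as a difference, for illustration only. If it is the true difference at both visits, the 2 × 3 main effect targets (0 + 2.84 + 2.84)/3 = 1.89 and the 2 × 2 main effect targets 2.84.

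**5. Group-by-time test.** With T0 as a level, the adjusted profile is (0, d1, d2), and the test of no interaction is the hypothesis 0 = d1 = d2, that is, no effect at all. In the 2 × 2 model it is d1 = d2. Rejection rates in 4000 simulated trials per row, 25 per arm, with assumed inputs:

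| Scenario | 2 × 3 | 2 × 2 |
|---|---|---|
| 0.6 SD at T1 and T2; correlations 0.6 with T0, 0.8 between T1 and T2 | 78% | 5% |
| 2.84 at T1 and T2 (2.84/3.1 = 0.92 SD); all correlations 0.6 | 99% | 5% |
| 2.84 at T1, none at T2; all correlations 0.6 | 98% | 94% |

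The 2 × 3 test rejects almost equally often for a constant effect and for one that has vanished by T2. The 2 × 2 test separates the two.

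**The case against.** The strongest reply is that 2 × 3 is probably a slip: the same section already describes the right structure, and correcting one digit removes the contradiction. That may be so, but the 2 × 3 statement is the operative instruction for the main model, and the sentence listing T0, T1 and T2 as the phases compared supports it. The text has to be corrected whichever was meant.

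Three stronger readings are tempting, and the documents do not support them.

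- **That the trial's reported effect and interval will be a third too small.** The protocol does not say that the averaged main effect, or any interval, is what will be reported. T0-adjusted differences at T1 or T2 (with the T0 slope free at each visit) and the t tests are not shrunk. The test of the group main effect keeps its p value, type I error and power. The t tests are not a full remedy, since they are not stated to be adjusted for baseline.
- **That 78% against 5% shows false positives.** It does not. The 78% is power to detect a real, constant effect under assumed inputs; the 5% is the null rate of a different hypothesis. The comparison shows only that the test has changed meaning. Persistence can still be judged from a group difference at T2.
- **That patients without T2 would be dropped, against the promise "Data from all randomized patients will be included in the analyses".** This assumes a fitting method that deletes incomplete cases. The article says mixed-model and names no such method, and the method for missing data may stand in a full protocol or analysis plan that is not shown.

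**Conclusion.** The specification is wrong as written and contradicts its own section. The 2/3 factor is exact for a group main effect averaged over the three levels. It rests on two conditions: that this average is what gets reported, and that the covariate is the T0 score of the outcome being analysed, as the section's description of the ANCOVA implies. The significance of that effect is not in question; its size is. The change in meaning of the group-by-time test follows from the model itself, while the rejection rates rest on the assumed effects, correlations and 25 per arm. Because this is the main model for the primary endpoint, it should be corrected before the final analysis.

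**What to change.** Replace 2 × 3 by a 2 × 2 ANCOVA: group by time, with time being T1 and T2 only and T0 as covariate, as the section already describes. State that the reported treatment effects are the T0-adjusted group differences with 95% CI at T1 and at T2. The group-by-time term then answers whether the effect changes between the two visits.

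Fitting this as a likelihood-based mixed model, which keeps patients who have T1 but no T2, is a sensible option and fits the stated aim of analysing all randomized patients; the correction does not depend on it.

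The cost is wording only. No assessment, visit or sample size changes, and the protocol places analysis of the complete dataset at the end of data collection.

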### Sample size

The sample size calculation was based on the results and the population variance from previous studies, which employed the BIT as a primary outcome measure [16, 17, 28, 32]. In particular, we calculated the sample size on the BIT (primary endpoint) using the following formula:
$$ N=\frac{2{\left({z}_{\left(1-\alpha \right)}+{z}_{\left(1-\beta \right)}\right)}^2{\sigma}^2}{\delta^2} $$where *N* is the final sample size; σ^2^: population variance established on previous studies [17] = 3.1; δ^2^: absolute error allowed for parameter estimation = 2.84; *z*: constant (corresponding to the value of the standardized normal random variable) that depends on the level of confidence desired for the estimation, fixing *α* = 0.05 and 1 − *β* = 0.80, (*Z*_1 − *α*_ + *Z*_1 − *β*_)^2^ = 10.5. The sample size resulting from the formula is 25.2. Consequently, the minimum sufficient simple to reach our primary outcome was established as 56 subjects (28 per group), to be enrolled over 2 years, assuming a 10% loss at follow-up.

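### Intention to treat is named as the answer to missing follow-up, but the between/within ANCOVA/ANOVA in its usual form would not include every randomized patient

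*Protocol article*

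**What the plan says.** The Statistical analysis section of the protocol article makes two statements about who is analysed. The general one is "Data from all randomized patients will be included in the analyses". The one on missing values is "Should data be missing at follow-up, data will be analyzed according to the intention to treat principle". The only other measure it mentions is a telephone call near follow-up to support retention.

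The same section names the models. If the assumptions hold, "a mixed-model ANCOVA will be used with a 2 × 3 design", with randomization group as the between factor, time of assessment as the within factor and T0 as covariate. If the regression slopes are not homogeneous, change scores go into a "2 × 2 mixed-model ANOVA with the between factor group and the within factor time (posttest and follow-up"). Alongside both: "In all cases, a two-tailed *t* test for independent samples will be employed to investigate the differences between groups". Software is named, but no procedure, estimation method, covariance structure, imputation or available-case rule.

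The Sample size section expects incomplete follow-up. It moves from 25.2 to 28 per group, 56 in total, "assuming a 10% loss at follow-up".

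**The concern.** Intention to treat is a rule about the analysis set and about arm assignment. It cannot stand in for a rule on an absent outcome, yet that is the job the sentence gives it.

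The models then pull the other way. Designs described by between and within factors, with a check of homogeneous regression slopes, are the language of classical split-plot ANOVA and ANCOVA. In its usual form that analysis needs every within-patient cell. A patient seen at T1 but not at T2 is left out of the whole model, including the T1 part, where the BIT was measured.

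Two things are at stake. The report could claim an analysis of all randomized patients that the main model does not deliver. And if the chance of missing T2 depends on how the patient was doing at T1, the remaining patients are a selected group, so the model's group contrast could be biased at both time points. T2 comes 12 weeks after T1, and the Ethical considerations section allows neglect treatment after the post-test if severe symptoms persist. A link between T1 status and later retention is therefore plausible, though the article gives no data on it.

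**Working it through.** **Inputs from the article.** Sample size section: constant 10.5, 3.1 (labelled a variance), 2.84 (labelled a squared difference), 25.2 from the formula, 28 per group and 56 in total, 10% loss. Statistical analysis section: 5% significance level, two-tailed t test.

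**1. The plan's own figure.** The formula is N = 2 × 10.5 × σ² / δ².
- With 3.1 as SD and 2.84 as difference: 2 × 10.5 × 3.1² / 2.84² = 25.02, close to the stated 25.2.
- With the labels taken literally: 2 × 10.5 × 3.1 / 2.84 = 22.9, which does not match.
- Inflation for loss: 25.2 / 0.90 = 28.0 per group, 56 in total. This reproduces.

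The SD-and-difference reading is used below, as an assumption. It gives d = 2.84 / 3.1 = 0.916.

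**2. Patients in the between/within model at the planned loss.** 56 × 0.10 = 5.6 patients without T2, and 56 − 5.6 = 50.4, so about 50 patients or 25 per group.

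**3. Precision of a T1 contrast restricted to those patients.** The standard error ratio is √(28 / 25.2) = 1.054, about 5% larger.

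**4. Power of a two-sample t comparison at T1, two-sided 0.05.**

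| Reading of 3.1 and 2.84 | d | 28 per group | 25 per group |
|---|---|---|---|
| SD and difference | 0.916 | 0.920 | 0.888 |
| Literal (variance and squared difference): √(2.84 / 3.1) | 0.957 | 0.940 | 0.912 |

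These figures are for a simple two-sample comparison. They show scale only; they are not the power of the ANCOVA, which also depends on correlations that the article does not give.

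**5. Heavier loss (assumed).** With 20% or 30% missing T2, the standard error ratio is 1.12 or 1.20. Normal-approximation power at d = 0.916 falls from 0.929 with everyone to 0.866 or 0.818 (0.902 at the planned 10%).

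**6. What selection could do (illustration only).** Assumptions not in the article: SD 3.1, true T1 effect 2.84, and missing T2 more likely with a worse T1 score, by 0.6 logits per unit. That is 0.6 × 3.1 = 1.86 logits per SD, a strong dependence. The simulation also assumed a T1–T2 correlation of 0.7, which does not affect the T1 contrast.

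| Missing T2 | Mean T1 effect, all T1 data | Mean T1 effect, only patients with T2 |
|---|---|---|
| 13% | 2.83 | 2.37 |
| 22% | 2.85 | 2.18 |

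The direction follows from the setup: the poorer scores are lost, and more of them are in the arm that does worse.

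**The case against.** The case against has several parts.

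- **Deletion is inferred.** A reader might conclude that the plan commits to dropping every patient without T2. The article does not say so. It never mentions listwise deletion or complete cases, it uses the label mixed-model, and deletion would contradict its own promise about all randomized patients. This stands: the claim is about what the named design does in its usual form. But nothing in the text specifies a likelihood-based model either, so the promise has no stated method behind it.
- **T1 data are not lost altogether.** A reader might also infer that these patients vanish from every T1 comparison. They need not: the independent-samples t test can use every T1 score. This stands, and it limits the point to the ANCOVA/ANOVA.
- **The loss is budgeted.** The sample size already allows for 10%, and the power after loss remains above the stated 0.80. This stands, so lost power is not the reason to act.
- **The bias is hypothetical.** Also true. The article contains nothing from which it could be estimated, and the illustration uses a strong assumed link. Nor does any text suggest carrying T1 values forward.
- **Missing-data detail belongs in an analysis plan.** It often does, and silence would not have been a finding. Here the article does address missing follow-up, and answers it with a principle that does not handle it. An analysis plan that repeated the sentence would carry the same gap.

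**Conclusion.** The point holds in a limited form. The article offers intention to treat as its answer to missing T2 and promises that all randomized patients are analysed, while naming between/within models that in ordinary use need complete data. Under that usual form, and at the plan's own 10% loss, about 50 of 56 patients would enter the model, and the all-randomized claim would not hold for it.

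The power cost is minor, about 0.92 to 0.89 for a two-sample T1 comparison on the SD-and-difference reading, and is already provided for. The substantive risk is selection bias, whose size cannot be derived from the article. The conclusion rests on reading the named models as classical split-plot analyses, which their wording supports but does not state.

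**What to change.** Replace the between/within ANCOVA/ANOVA with a likelihood-based linear mixed model in which T1 and T2 are the outcomes and the fixed effects are group, time, group × time, baseline BIT and baseline × time. Fit it to all available post-baseline data, each patient in the assigned arm, so that a patient with T1 but no T2 still contributes.

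State that the model is valid under missing at random. Patients with no post-baseline BIT add no outcome information even here, so report how many randomized patients that is, by arm, and word the all-randomized statement accordingly. Add one sensitivity analysis that departs from missing at random for T2, for example by shifting the missing T2 values by a stated amount.

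The cost is a paragraph of text and slightly more analysis work. Recruitment, treatment and visits do not change. The Trial status section reports ten patients randomized at the time of writing, so the change could be fixed well before the final analysis.

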### Oversight and monitoring

A dedicated member of the investigator team other than the PI will assess the completeness of data collection and be involved in monitoring all the clinical trial’s organizational, ethical, and scientific aspects. The PI will declare the end of the enrolment.

### Dissemination plans

All data will be treated so that the participants’ identities will be kept anonymous. Before publication, the trial results will be discussed within the research group, and authorship eligibility will be agreed upon with all contributors before publication. Professional writers will not be involved in the dissemination process. The trial data, suitably anonymized, will be made available upon request at the end of the trial.

### Ethical considerations

Treatments for LHN will be allowed after the post-test, should severe LHN-related symptoms persist. Furthermore, during the trial, the standard care treatments will be guaranteed within the inpatient rehabilitation setting for all patients in the r-TMS intervention and SHAM control groups.

### Roles and responsibilities

Patients are being enrolled within two centers: the Neuro-rehabilitation Unit of IRCCS Istituto delle Scienze Neurologiche di Bologna (which is the coordinating center) and the Intensive Rehabilitation Unit of “Villa Bellombra Hospital” in Bologna. Both centers received the required ethical approvals and authorizations from the local ethics committee (CE/AVEC num. 0078006 and CE/AVEC num. 148456).

## Discussion

Within the SMART-ATLAS study, we propose a new combined protocol for the rehabilitation of LHN in right hemispheric stroke patients. In particular, it combines two potentially effective treatments for the rehabilitation of cognitive and behavioral symptoms of left hemispatial neglect to investigate the advantages of a combined protocol compared to a single intervention. We will also combine brain stimulation (inhibitory r-TMS on the left intact parietal cortex) with a cognitive treatment (visual scanning), which will follow the stimulation. 

Many published studies have highlighted the efficacy of the brain stimulation and cognitive treatments administered alone for the rehabilitation of LHN syndrome after stroke [23]. However, the level of scientific evidence for the efficacy of combined approaches (i.e., brain stimulation and cognitive treatments) is still low because of factors such as small sample size, methodological bias (lack of double-blind studies or follow-up assessments), and contradictory results. To control for these biases, we will apply a double-blind, SHAM-controlled design within the context of an RCT, in which assessors and patients are blinded to the type of stimulation used, reducing any source of potential bias. Moreover, our outcomes consider several construct domains related to LHN. Indeed, we consider cognitive and behavioral aspects of LHN, together with disabilities in the motor domain and the activity of daily living. Importantly, we introduce indexes based on neurophysiological data to monitor changes induced by the treatment at a neurophysiological level. Thus, our design can provide a valuable comparison between the combined approach and the cognitive treatment alone, thus evidencing specific brain stimulation effects and contributing to identifying the most beneficial rehabilitation approach for LHN patients.

This study’s central hypothesis is that clinical symptoms of LHN are correlated to an imbalance in interhemispheric activity due to hyperactivity of the left hemisphere [1, 10–12]. Inhibitory r-TMS on the intact left parietal cortex reduces the left hemisphere activation and can rebalance interhemispheric activity. Therefore, this RCT will provide evidence of the clinical efficacy of the rebalancing effect of the r-TMS on a larger sample of stroke patients. In particular, we expect to observe better performances on clinical tests and batteries, indicating more substantial improvements in cognitive and behavioral symptoms of LHN in the r-TMS group compared to the control SHAM group. Furthermore, we expect that these more significant clinical improvements in the r-TMS group can also be reported in specific scales assessing motor independence in the activities of daily living. Finally, inhibitory r-TMS on the intact left parietal cortex could point out the particular effect of r-TMS protocols on neurophysiological correlates of LHN. More in detail, we expect to observe in the r-TMS group a more significant rebalancing effect than in the control group, as demonstrated by smaller amplitudes of vABI and earlier latencies of IHTTs at the post-test assessment. Finally, we expect to observe the persistence of this effect at follow-up.

Although both the visual scanning training and the r-TMS protocols alone have been demonstrated to be effective in the rehabilitation of clinical symptoms related to LHN, combinations of different therapies may boost the therapeutic effect. The rationale behind this hypothesis is that following a right hemisphere stroke, the neuronal loss may impair cognitive functions due to a functional deactivation of the related neuro-functional networks. Thus, the reactivation of those networks can support the rehabilitation of the compromised functions [40, 41]. Indeed r-TMS can lead to neuronal activity changes that outlast the stimulation itself and enable empowerment of a specific network or neuronal circuit [40]. This after-effect of the r-TMS can support cognitive task execution, thus facilitating experiential learning during cognitive training [40, 41]. In our study, inhibitory r-TMS is applied over the intact left parietal cortex; thus, the r-TMS modulation concerns the preserved areas and the interhemispheric connectivity [42–44]. As a consequence, r-TMS could increase the “responsiveness” of the peri-lesional areas and the interhemispheric connectivity [43] during a cognitive training protocol (i.e., the visual scanning), increasing its effectiveness compared to the SHAM condition, where only a placebo stimulation is applied before the training.

